## 2.7 Analyses

One-way analysis of covariance (ANCOVA), with sex as a covariate, will be used to compare learning rates between the 3 groups. ANCOVA, controlling for the pre-training value, will be used to compare the following outcomes between the 3 groups at the post-training and retention time points: average number of steps, step initiation time, step execution time, step length, braking impulse, margin of stability, mini-BEST, and FES-I. Pre-planned contrasts will be used to compare outcomes between the high- and moderate-intensity groups, and between the two RBT groups combined and the walking control group. Alpha will be 0.05 for the primary outcome (learning rates), and adjusted for multiple comparisons using the Holm-Bonferroni method for secondary outcomes. Falls and quality of life data will be reported without inference so that these data can be used in meta-analyses and/or as pilot data for future studies.

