## 2. METHODS TO BE USED

### 2.1 Trial design

This study is an outcome-adjudicator blinded randomized controlled trial, following motor learning protocols (Figure 1). People with chronic stroke (n=63) will be randomly assigned to: 1) high-

intensity RBT, 2) moderate-intensity RBT, or 3) a walking control group. Training sessions will take place on four consecutive days; reactive stepping will be assessed pre-training, at the end of each training session (to determine the rate of adaptation), and after a delay of one week (to determine retention of learning effects) using a novel untrained perturbation. Falls in daily life, physical activity, and participation will be assessed for 12 months post-training.

| Baseline
Day 1                                                                                                   | Training sessions
Days 2-5                                                                                                                                                              | Retention
Day 12                                                   | Falls monitoring
0-12 months post-training | Follow-up
12 months post-training |
|----------------------------------------------------------------------------------------------------------------------------|---------------------------------------------------------------------------------------------------------------------------------------------------------------------------------------------------|------------------------------------------------------------------------------|------------------------------------------------------|---------------------------------------------|
| Multi-step threshold
3 backward-fall perturbations
Mini-BEST, FES-I, EQ-5D-5L, fear of falling
Cohort descriptors | 
High-intensity RBT
3 backward-fall perturbations
 
Moderate-intensity RBT
3 backward-fall perturbations
 
Walking practice
3 backward-fall perturbations
 | 3 backward-fall perturbations
Mini-BEST, FES-I, EQ-5D-5L, fear of falling | Falls in daily life                                  | FES-I, EQ-5D-5L, fear of falling            |

**Figure 1: Overview of the trial design.** Mini-BEST=mini-Balance Evaluation Systems Test; FES-I=Falls Efficacy Scale-International; EQ-5D-5L=EuroQoL 5-level quality of life measure; RBT=reactive balance training

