### 2.3 Group allocation and blinding

Participants will be assigned using blocked (block size 6 or 9) randomization (computer-generated random sequence), stratified by sex to one of the three training groups. Participants cannot be blinded to group allocation for exercise trials. The primary outcome will be obtained during the training sessions and will be scored by a blinded adjudicator from raw data (videos). Secondary outcomes will be obtained by a blinded research assistant. To maintain allocation concealment, group allocation will be performed centrally by the principal investigator, who will not be involved in recruiting.

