### 2.8.1 Primary outcome: balance reactions to an untrained perturbation

Responses to backward-fall perturbations will be assessed at the end of each session, and at the one-week retention time-point. An untrained perturbation (i.e., backward-fall perturbation) will be used to test transfer of learning to a novel context. To prevent participants from pre-planning their responses, the backward-fall perturbations will be completed in block of trials with 6 low-magnitude forward-fall and lateral perturbations (25-50% of participants' multi-step threshold), presented in an unpredictable sequence. Improved reactive stepping with practice of forward-fall perturbations transfers to reactions to backward-fall perturbations in people with chronic stroke. Participants will experience 3 forward-directed platform translations, evoking a backward loss of balance, at the multi-step threshold. Because backward falls are more challenging than forward or lateral falls, a backward-fall perturbation at the forward-fall multi-step threshold should evoke a multi-step reaction, at least prior to training. Testing at each participant's multi-step threshold ensures that participants will initially experience challenges responding to the perturbation and there is room for improvement with training. The primary outcome will be number of steps taken to recover balance. Extra steps are required when the first step is ineffective for regaining balance; less effective initial steps require more extra steps. Multi-step reactions are associated with increased risk of falls in daily life, and people reduce the number of steps taken to recover balance after RBT. Therefore, number of steps taken to recover balance is a global indicator of effectiveness of balance reactions.

We will calculate the learning rate for each participant by fitting an exponential function,  $a + b \left( e^{-\frac{t}{x}} \right)$ , to their data (average number of steps taken at each assessment time point), where  $a$  and  $b$  are constants,  $t$  is the assessment time point, and  $x$  is the learning rate. Figure 4 illustrates possible results for the three groups, using three different learning curves ( $x=0.4$ , 2 and 10 for the high-intensity, moderate-intensity, and walking control groups, respectively).

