## 2.6 Sample size justification

Our primary outcome is learning rate. The sample size for each group was estimated as  $\lambda/\Delta$ , where  $\lambda$  was obtained from tables for 3 groups using probability of a Type 1 error ( $\alpha$ ) of 0.05, probability of a Type II error ( $\beta$ ) of 0.2; therefore,  $\lambda$  of 9.64 was used. Additionally:

$$\Delta = \frac{1}{\sigma^2} \sum_{i=1}^k (\mu_i - \bar{\mu})^2$$

where  $\sigma$  is the standard deviation,  $k$  is the number of groups (3),  $\mu_i$  is the mean for each groups and  $\bar{\mu}$  is the mean for all groups combined. From pilot data, we estimate a standard deviation of 9.7 for the learning rate. People with stroke typically require 3-4 steps to regain stability following the perturbation magnitudes used in the proposed study. Due to the mechanical challenges of the perturbation, at minimum 1 step is required to respond to the perturbation (i.e., young healthy adults would take 1 step to respond to the perturbation). Therefore, an improvement from 3-4 steps pre-training to 1-2 steps post-training is considered clinically meaningful, and a much larger effect size would likely not be possible. From previous studies an improvement from taking, on average, 3-4 steps pre-training to 1-2 steps post-training is feasible. Simulating learning rates between these data points (Figure 5), we expect that learning rates of approximately 0.4 ( $\mu_1$ ), 2 ( $\mu_2$ ) and 10 ( $\mu_3$ ) for the high-intensity, moderate-intensity, and walking control groups, respectively, would show meaningful differences between the three groups. Therefore,  $\Delta$  was calculated as 0.56, giving a target sample size of 17 per group or 51 participants total. To account for a ~20% rate of withdrawal, we will aim to recruit 21 participants per group, or 63 participants total. Enrolment will stop when 51 participants have completed the retention test, or 63 participants have been enrolled, whichever happens first.

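### The primary learning-rate ANCOVA is valid, but it adjusts for sex only; adding the Day 1 backward-fall step count as a prespecified covariate would cost almost nothing and may gain a little power.

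*Protocol*

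**What the plan says.** All of this is in the protocol.

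- **Primary model (section 2.7, Analyses):** "One-way analysis of covariance (ANCOVA), with sex as a covariate, will be used to compare learning rates between the 3 groups". Sex is also the stratification factor in section 2.3, where allocation is "stratified by sex to one of the three training groups".
- **Other tested outcomes (section 2.7):** "ANCOVA, controlling for the pre-training value, will be used to compare the following outcomes between the 3 groups". These are average number of steps, the stepping and stability measures, mini-BEST and FES-I.
- **Contrasts (section 2.7):** "Pre-planned contrasts will be used to compare outcomes between the high- and moderate-intensity groups", and between the two RBT groups combined and walking.
- **What is measured before training (section 2.1, Trial design):** "reactive stepping will be assessed pre-training, at the end of each training session". Figure 1 lists three backward-fall perturbations on Day 1.
- **How the learning rate is obtained (section 2.8.1):** the curve a + b·exp(−t/x) is fitted for each participant to "their data (average number of steps taken at each assessment time point"), and x is the learning rate.

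The protocol gives no correlation between Day 1 steps and x, and it does not explain why the primary model uses a different covariate set.

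**The concern.** In a randomised comparison with about 17 analysed per arm, a covariate that is measured before training and predicts the outcome reduces residual variance. Day 1 step count is a natural candidate. It is already collected, and x is derived from the series that starts with it.

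Using Day 1 as a point on the fitted curve is not the same as adjusting for it. The constants a and b are free, so x is not conditioned on the starting level. Noise in a three-trial average can also pass into x: a high Day 1 average by chance makes the first drop look steep and x small.

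What is at stake is some precision in the primary comparison, where power on the protocol's own inputs is slightly below the intended 80%.

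**Working it through.** **Inputs from section 2.6:** means 0.4, 2 and 10; SD 9.7; α 0.05; β 0.2; tabulated λ 9.64; 17 per group.

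**The protocol's own figure**

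- Overall mean = (0.4 + 2 + 10)/3 = 4.133.
- Sum of squared deviations = 13.94 + 4.55 + 34.42 = 52.91.
- Δ = 52.91/9.7² = 52.91/94.09 = 0.562 (stated 0.56).
- n = 9.64/0.562 = 17.14 per group (stated 17). This is reproduced to within rounding, and it assumes no baseline adjustment.

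**Power of the model as written**

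- Noncentrality = 17 × 0.5623 = 9.56.
- Error df = 51 − 3 − 1 = 47, with sex as the one covariate and no variance reduction credited to it.
- Noncentral F gives 76.9%.

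**Power with Day 1 steps added**

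Residual variance becomes 9.7²(1 − r²), so noncentrality = 9.56/(1 − r²), with 46 error df. Here r is the size of the pooled within-arm correlation between Day 1 steps and x. It is an assumption, shown as a range.

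| r | Noncentrality | Omnibus power |
|---|---|---|
| 0 | 9.56 | 76.8% |
| 0.1 | 9.66 | 77.3% |
| 0.2 | 9.96 | 78.6% |
| 0.3 | 10.50 | 80.9% |

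**Planned contrasts (noncentral t)**

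- RBT groups combined versus walking: 84.9% with sex only, 88.0% at r = 0.3.
- High versus moderate: 7.6% at r = 0, 7.8% at r = 0.3.

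**What r might be**

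The per-participant fit was simulated under assumed inputs: five time points (Day 1 and four sessions), three integer step counts per point with a minimum of 1, a start of 3.5 steps and an end of 1.5, trial SD 0.5 to 1.0, and between-person baseline SD 0 to 0.6.

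- The pooled within-arm correlation was about −0.16 to −0.27, which in the formula above is a gain of about 1 to 3 points.
- Simulating the whole path from step counts through fitted x to the ANCOVA gave a change of about −1 to +1 point, with type I error essentially unchanged.
- Single-arm correlations can be larger (about −0.4 or beyond), but the ANCOVA works with the pooled value.

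**Chance imbalance**

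If two arms of 17 differ on Day 1 by one standard error, the unadjusted difference in x moves by r × 9.7 × √(2/17) = 3.33r. That is 0.33 at r = 0.1 and 1.0 at r = 0.3. The planned high–moderate difference is 2 − 0.4 = 1.6. The shift has expectation zero over randomisations, and the unadjusted standard error already reflects it.

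**The case against.** The strongest reply is that nothing here is wrong, and most of that reply stands.

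- **Apparent inconsistency.** A reader might infer that section 2.7 contradicts itself by baseline-adjusting every tested outcome except the primary one. It does not. Each of the other outcomes uses its own pre-training value, so step count is the covariate only for step count. A learning rate has no pre-training value.
- **Imbalance as bias.** A reader might also infer that chance differences in starting ability bias the primary test. They do not. Under randomisation they add variance and conditional error, but no bias and no inflation of type I error. The model already includes the stratification factor, and the comparison of step counts at retention (the third hypothesis) is already adjusted for baseline.
- **Size of the gain.** Powers of 88.1% (omnibus) and 93.2% (RBT combined versus walking) can be computed, but they need r = 0.5. The pooled correlations in the simulations are well short of that.
- **Limits of the simulation.** Fitted x had SDs of about 17 to 24 in two arms against the protocol's 9.7, and its slope on Day 1 steps differed several-fold between arms. A common-slope model is therefore only an approximation, and no firm gain can be quoted for this trial.
- **Shared data.** Day 1 steps are among the data from which x is fitted, so part of any correlation is shared measurement error. That does not make the covariate invalid, because it precedes training, but declining it is a defensible choice.

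What survives is the narrow point: a suitable covariate is collected, fitting the curve through it does not adjust for it, and adding it carries almost no penalty.

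**Conclusion.** The point holds as a minor efficiency suggestion. The primary ANCOVA in section 2.7 is valid as written, and no stated figure depends on baseline adjustment; the 17 per group was derived without it.

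If r is between 0 and 0.3, adding Day 1 steps moves omnibus power from 76.9% to between 76.8% and 80.9%. The simulations point to the lower part of that range, about 0 to 3 points and possibly nothing. The change does not help the first-listed hypothesis, since power for high versus moderate stays near 8%.

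This rests on the protocol's means and SD, on an r that the protocol does not give, and on Day 1 steps being unaffected by allocation. The baseline session precedes the first training session, but the protocol does not say whether participants know their group by then.

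**What to change.** In section 2.7, before any outcome data are seen, specify that the learning-rate ANCOVA has sex and the Day 1 average number of backward-fall steps as covariates, and use the same two covariates for both planned contrasts.

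No new data are needed. The cost is one sentence and one error degree of freedom (47 to 46), which is about 0.1 point of power if the correlation is zero. The choice should be fixed in advance so that it cannot depend on the results. The sample size needs no change on this account, and no gain from the covariate should be credited in it.

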## 2.5 Outcome measures

Outcome assessment will be repeated one week after the end of the training program to assess retention of training effects. Falls will be assessed for 12 months post-training.

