to mail to the research team every month for 1 year post-training. Postcards will contain a calendar, on which participants will record falls. The blinded research assistant will call participants who do not return the postcard to determine if any falls occurred. The research assistant will also contact participants reporting a fall to complete a short questionnaire determining the cause and consequences of the fall (e.g., injuries; Appendix E). This method is considered the ‘gold standard’ for fall reporting and has been successfully used by our team. The 5-level EuroQoL health status measure (EQ-5D-5L) asks participants to rate their health in five dimensions (mobility, self-care, usual activities, pain/discomfort, and anxiety/depression) on a five-point scale and their overall health state on a scale from 0-100. The EQ-5D-5L has good-to-excellent test-retest reliability across several populations (ICC: 0.69-0.93). The FES-I asks participants to rate their concern about falling while performing 16 everyday tasks. The FES-I shows excellent test-retest reliability (ICC=0.97) in people with chronic stroke. Fear of falling and activity curtailment due to fear of falling will be assessed with two questions (“are you afraid of falling?” and “do you think fear of falling has made you cut down on any activities that you used to do?”).

The mini-BEST, EQ-5D-5L, FES-I, fear of falling, and activity curtailment due to fear of falling will be assessed pre- and post-training. Additionally, the EQ-5D-5L, FES-I, fear of falling, and activity curtailment due to fear of falling will be repeated via telephone at the end of the 1-year falls monitoring period (Figure 1).

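### Sex, the stratification factor, is in the learning-rate ANCOVA but is not named for the other eight ANCOVA outcomes, including steps at retention

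*Protocol*

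**What the plan says.** Section 2.3 of the Protocol describes blocked randomisation, "stratified by sex to one of the three training groups".

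Section 2.7 then gives two models in consecutive sentences:

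- For the primary outcome: "One-way analysis of covariance (ANCOVA), with sex as a covariate, will be used to compare learning rates between the 3 groups".
- For everything else that is tested: "ANCOVA, controlling for the pre-training value, will be used to compare the following outcomes between the 3 groups". The list has eight entries: average number of steps, step initiation time, step execution time, step length, braking impulse, margin of stability, mini-BEST and FES-I. Sex is not mentioned.

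The second sentence also sets the timing, "at the post-training and retention time points: average number of steps" being the start of the list. Average steps at retention is the quantity in primary hypothesis 3 (section 1.2).

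On when mini-BEST and FES-I are collected, the document says three things. Figure 1 (section 2.1) puts "Mini-BEST, FES-I, EQ-5D-5L, fear of falling" in the baseline and Day 12 retention columns, and lists only the training and the backward-fall perturbations for Days 2-5. Section 2.5 says: "Outcome assessment will be repeated one week after the end of the training program to assess retention of training effects". Section 2.8.2 says: "The mini-BEST, EQ-5D-5L, FES-I, fear of falling, and activity curtailment due to fear of falling will be assessed pre- and post-training". Section 2.8.2 and Figure 1 add a further FES-I at 12 months.

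**The concern.** When randomisation is stratified, the groups are balanced on the stratification factor by design. If the analysis ignores a factor that predicts the outcome, its variance stays in the error term although it no longer contributes to chance differences between groups. The reported standard errors are then larger than the design warrants. The Protocol recognises this for learning rate, but its next sentence specifies a different covariate set for the same randomisation. That second set serves one of the three primary hypotheses. At stake is some precision in a trial planned on 51 completers.

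The timing wording is a separate, smaller matter. For mini-BEST and FES-I it is unclear which visit, or how many visits, the ANCOVA refers to, and the 12-month FES-I has no stated role.

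**Working it through.** **The plan's own figure.** No stated number is in dispute, but the sample size fixes the degrees of freedom. Section 2.6 gives means 0.4, 2 and 10, SD 9.7 and λ = 9.64. The mean is 4.133, the squared deviations sum to 13.94 + 4.55 + 34.42 = 52.91, and Δ = 52.91/9.7² = 0.562 (stated 0.56). Then n = 9.64/0.562 = 17.1 per group, which agrees with the stated 17 apart from rounding down. That gives 51 completers.

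**Cost of adding sex.** With 51 completers, three groups and a baseline covariate, residual degrees of freedom are 51 − 3 − 1 = 47. With sex they are 46. As a gauge of what one degree of freedom costs, noncentral-F power for the learning-rate comparison on the plan's inputs is 76.95% without sex and 76.89% with it, if sex explains nothing.

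**Effect on the standard error.** Let r² be the share of residual variance, after baseline adjustment, that sex explains. The Protocol gives no value, so r² is an assumption. With groups balanced on sex, the ratio of standard errors, sex omitted to sex included, is 1/√(1 − r²):

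| Assumed r² | Ratio | Excess |
|---|---|---|
| 2% | 1/√0.98 = 1.010 | 1% |
| 5% | 1/√0.95 = 1.026 | 3% |
| 10% | 1/√0.90 = 1.054 | 5% |

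**Effect on error rates.** A simulation of the contrast of both RBT groups with control used 51 participants, allocation balanced within sex, and 6,000 runs per cell. Its other inputs are assumptions that are not in the Protocol: a 30/21 sex split, baseline correlation 0.5 and a treatment effect of 0.75 SD.

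| Sex effect (SD) | Type I, omitted | Type I, included | Power, omitted | Power, included |
|---|---|---|---|---|
| 0 | 5.5% | 5.4% | 81.3% | 81.1% |
| 0.3 | 4.2% | 4.4% | 79.8% | 80.6% |
| 0.5 | 4.0% | 4.9% | 78.8% | 81.3% |
| 0.8 | 3.4% | 5.2% | 75.7% | 81.5% |
| 1.0 | 2.9% | 5.5% | 71.5% | 80.9% |

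The Monte Carlo standard error near 5% is √(0.05 × 0.95/6000) = 0.3 percentage points, so the departures from 5% in the columns with sex included are within about two standard errors.

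To link the two tables: the residual variance without sex is 1 − 0.5² = 0.75, and sex adds b² × (30 × 21/51²) = 0.242b². Ignoring the slight correlation of sex with baseline, effects of 0.3, 0.5, 0.8 and 1.0 SD correspond to r² of roughly 0.022/0.772 = 3%, 0.061/0.811 = 7%, 0.155/0.905 = 17% and 0.242/0.992 = 24%. The assumed range of 2% to 10% therefore covers the 0.3 and 0.5 SD rows, where the power loss is about 1 to 3 points.

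**Time points.** Section 2.7 treats post-training and retention as two occasions. For steps and the stepping-mechanics outcomes both exist, because backward-fall responses are recorded at the end of each session and at one week (sections 2.8.1 and 2.8.2). For mini-BEST and FES-I, Figure 1 and section 2.5 give one repeat around training, at Day 12. Section 2.8.2 calls the repeat post-training and refers to Figure 1. Either its post-training visit is Day 12, and section 2.7 names one occasion too many for these two scales, or Figure 1 omits an assessment.

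**12-month FES-I.** Section 2.8.2 exempts FES-I from the core-set outcomes that will not be analysed. Section 2.7 analyses it at post-training and retention only, and its statement on reporting without inference covers falls and quality of life. The 12-month value falls under neither.

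**The case against.** The strongest reply is that the designated primary outcome already adjusts for sex, that section 2.7 does not say the pre-training value is the only covariate, and that full covariate lists are often left to an SAP, which is not at hand. The effect is also modest: no document suggests that sex matters strongly after baseline adjustment, and the material power losses appear only at 0.8 to 1.0 SD. All of this stands as to size. It does not remove the point, because two adjacent sentences name different covariates for one randomisation, and the second covers a primary hypothesis. Silence on the 12-month FES-I is likewise something an SAP could settle.

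A reader might infer more than the text supports:

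- **That mini-BEST and FES-I are definitely not collected post-training.** Section 2.8.2 uses that very term for them, so this is an inconsistency, not proof of non-collection.
- **That naming uncollected time points inflates the Holm-Bonferroni family.** A test without data yields no p-value, and section 2.7 does not fix the number of tests.
- **That the learning-rate model should also adjust for pre-training steps.** Learning rate is fitted to the step counts at each assessment, and the pre-training count is apparently one of them. It is an input to the curve rather than a separate baseline, so adjusting for it is debatable.
- **That every secondary outcome is affected.** Adverse outcomes, falls and quality of life are outside that ANCOVA sentence.

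**Conclusion.** The point holds as a modest one. Sex, by which randomisation is stratified, is missing from the stated model for the eight outcomes in the second ANCOVA sentence, including retention steps under primary hypothesis 3. If sex is prognostic after baseline adjustment, the tests are conservative and lose some precision: standard errors are about 1% to 5% too large for an assumed 2% to 10% of residual variance. If sex is not prognostic, nothing visible is lost either way. A reader might infer bias or false-positive risk from the omission. The calculations show neither, since type I error falls below 5% as the sex effect grows. The sizes rest on assumed variance shares and, for the simulation, on an assumed sex split, baseline correlation and effect.

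The time-point wording is a secondary inconsistency between sections 2.1 (Figure 1), 2.5, 2.7 and 2.8.2. The 12-month FES-I is a gap in detail.

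**What to change.** In section 2.7, specify group, pre-training value and sex as the terms of every ANCOVA in the second sentence. Leave the learning-rate model unchanged. The cost is a few words and one residual degree of freedom per model (47 to 46 at 51 completers).

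In the same edit, reconcile Figure 1 and sections 2.5, 2.7 and 2.8.2 on when mini-BEST and FES-I are assessed, and list the analysis time points by outcome. Add one sentence saying whether the 12-month FES-I will be tested or only described. If an SAP exists, it should carry the same wording. If Day 12 is the only intended repeat visit around training, no change to data collection is needed.

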## 2.2 Trial interventions

Training sessions will be overseen by a physiotherapist and will last for 1 hour over 4 consecutive days. Training will occur using the ‘FallsLab’ custom-built 6m x 3m motion platform (Figure 2). A robotic safety harness gantry allows participants to move freely on the platform, but prevents falls if they are unable to regain balance. An accelerometer (Series 7523A, Dynamic Transducers and Systems, Chatsworth, California, USA) placed on the platform records platform acceleration. Eight high-resolution video cameras will be positioned around the room to collect markerless 3-dimensional kinematic data (Theia Markerless, Inc., Kingston, ON). Four force plates on the platform (1.5m x 1.5m, model BP11971197-2000, Advanced Mechanical Technology, Inc., Watertown, Massachusetts, USA) record forces and moments in 3 dimensions.

A baseline data collection session will be completed before the first training session. The forward multi-step threshold will be determined, using a staircase procedure. Participants will initially experience a backward-directed platform perturbation (causing a forward ‘fall’) at 0.5 m/s peak acceleration (intensity). Participants will be instructed to do whatever they need to do to recover balance but, if they need to take a step, to minimize the number of steps taken. If participants do not step or only take a single step to recover balance, the intensity will be increased in 0.5 m/s increments until the participant needs to execute a multi-step reaction to recover balance. The intensity will then be reduced in 0.25 m/s increments until the participant only takes one step (first reversal). The intensity will be increased, and then decreased, in 0.25 m/s increments, reversing when the participant’s step response changes (i.e., single- or multi-step reaction) until there are four reversals (Figure 3). The multi-step threshold is the highest perturbation magnitude where the participant can recover balance with a single step. The multi-step threshold should be around 2-3 m/s, which will take approximately 10-16 trials to determine.

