Participants assigned to the RBT groups will experience 36 multi-directional (left-, right-, and forward-fall) perturbations in each training session, presented in an unpredictable sequence. Participants assigned to **high-intensity RBT** will experience perturbations at 150% of the multi-step threshold; for example, for a multi-step threshold of 2 m/s the high intensity will be 3 m/s.

[figure not shown]

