**Figure 2: FallsLab motion platform and apparatus.**

Participants assigned to the **moderate-intensity RBT** group will experience perturbations at the multi-step threshold. If participants respond to the perturbations with a single step (high intensity group) or no step (moderate intensity group) in >50% of trials, the intensity will be increased by 25% in the subsequent training session. Participants in the **walking control** group will complete 36 unperturbed walking trials on the FallsLab platform in each training session.

[figure not shown]

**Figure 3: Example of the staircase procedure to determine the multi-step threshold.** The first multi-step reaction is observed at 2.5m/s, at which point the intensity (peak acceleration) is reduced until a single step is observed. The perturbations are increased and decreased in 0.25m/s increments until there are four reversals of the ‘staircase’.

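### The primary learning-rate ANCOVA adjusts for sex only and leaves out the baseline multi-step threshold, a possible loss of efficiency (not a bias) that one phrase in section 2.7 would address

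*Protocol*

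**What the plan says.** **Measurement.** Protocol section 2.2: "A baseline data collection session will be completed before the first training session", and in it "The forward multi-step threshold will be determined, using a staircase procedure". Every participant therefore has a threshold before training starts. On its expected size: "The multi-step threshold should be around 2-3 m/s"² (the unit is m/s²).

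**Use in training.** Also in section 2.2, the high-intensity arm "will experience perturbations at 150% of the multi-step threshold", while the moderate-intensity "group will experience perturbations at the multi-step threshold". The walking control "group will complete 36 unperturbed walking trials on the FallsLab platform in each training session", so the threshold sets no training intensity there.

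**Use in testing.** Section 2.8.1 delivers the backward-fall test at each person's threshold. The reason given is that testing at each participant's "multi-step threshold ensures that participants will initially experience challenges responding to the perturbation".

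**Use in analysis.** Section 2.7 names sex as the covariate for learning rate, the primary outcome. For average steps, the stepping-mechanics outcomes, mini-BEST and FES-I, "ANCOVA, controlling for the pre-training value, will be used to compare the following outcomes between the 3 groups". The threshold appears in neither model. Section 2.3 stratifies the randomisation by sex only.

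**The concern.** The threshold is the trial's own graded measure of reactive balance ability, taken before training and already in the data. The secondary models at least carry the baseline value of their own outcome. The learning-rate model has no counterpart, because a fitted rate has no pre-training value, and sex is its only adjustment.

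If learning rate is related to the threshold, that variation stays in the error term of the primary analysis. At 17 completers per group the design has little slack, so even a modest reduction in residual variance could matter. With thresholds expected between 2 and 3 m/s², absolute test acceleration can differ by half between participants (3/2 = 1.5), so a relation is plausible.

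**Working it through.** **Inputs (protocol section 2.6).** Expected learning rates 0.4, 2 and 10; SD 9.7; alpha 0.05; beta 0.2; lambda 9.64; 17 per group, 51 in total. Not given anywhere: the partial correlation r between threshold and learning rate. It is taken as an assumption over a range from 0 to 0.6.

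**1. Reproduce the plan's figure.** The mean of the three rates is 12.4/3 = 4.133.

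Delta = [(0.4 − 4.133)² + (2 − 4.133)² + (10 − 4.133)²] / 9.7² = (13.94 + 4.55 + 34.42) / 94.09 = 52.91 / 94.09 = 0.562.

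9.64 / 0.562 = 17.1, which agrees with the stated 17 per group.

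**2. Omnibus power as planned.** Noncentrality = 17 × 0.562 = 9.56. From the noncentral F with 2 and 47 df (51 less three groups and sex), power is 0.769.

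**3. Omnibus power with the threshold added.** Residual variance is multiplied by (1 − r²), so noncentrality = 9.56 / (1 − r²), with 46 error df. The equivalent total sample is 51 / (1 − r²).

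| r (assumed) | 1 − r² | Omnibus power | Equivalent total n |
|---|---|---|---|
| 0 | 1.00 | 0.768 | 51 |
| 0.1 | 0.99 | 0.773 | 52 |
| 0.2 | 0.96 | 0.786 | 53 |
| 0.3 | 0.91 | 0.81 | 56 |
| 0.4 | 0.84 | 0.84 | 61 |
| 0.5 | 0.75 | 0.88 | 68 |

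**4. The cost that step 3 leaves out.** The table counts the lost degree of freedom but not the average inflation of contrast variance from estimating one more slope. That factor is about 47/46 = 1.022. The net variance factors are then:
- r = 0: 1.02
- r = 0.3: 0.91 × 1.022 = 0.93
- r = 0.4: 0.84 × 1.022 = 0.86
- r = 0.5: 0.75 × 1.022 = 0.77

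If noncentrality is divided by this factor too, power is about 0.76, 0.80, 0.83 and 0.87 in turn. Break-even is where (1 − r²) × 1.022 = 1, that is |r| of about 0.15.

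**5. The planned contrasts (noncentral t).** For the two RBT arms combined against control (difference 10 − 1.2 = 8.8), power is 84.9% without the threshold, 88.0% at r = 0.3 and 93.2% at r = 0.5. For high against moderate (difference 1.6), it is 7.6% without, 7.8% at r = 0.3, 8.5% at r = 0.5 and 9.1% at r = 0.6.

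**6. Is anything biased?** With 17 per arm, the chance difference in mean threshold between the high and moderate arms has an SD of √(2/17) = 0.34 threshold SDs. An imbalance of that size shifts the learning-rate contrast by r × 0.343 × 9.7: 0.33, 1.0 or 1.7 at r = 0.1, 0.3 or 0.5. The standard error of the contrast is 9.7 × √(2/17) = 3.33, and it already contains this variation. In 10,000 simulated null trials at each of r = 0, 0.3 and 0.5, type I error was 5.0–5.4% both with and without the covariate.

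**The case against.** **The covariates are a legitimate choice.** Sex is the stratification factor, and adjusting for the pre-training value is standard. Nothing in section 2.7 is misstated, and further covariates are often left to a statistical analysis plan. This stands in part: the omission is not an error. But section 2.7 does name the covariate of the primary model, so a suggestion to extend it belongs there.

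**The gain rests on an unknown correlation.** This stands. Two features of the design could also keep it low. Scaling the test to each person's threshold already standardises difficulty, before and after training. And learning rate is fitted with separate constants for level and amplitude in each participant, so differences in starting ability need not reach the rate.

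**The secondary models already carry much of the threshold.** This stands too. For step count and stepping mechanics, the pre-training value comes from the same backward-fall test at the same individual magnitude. An over- or underestimated threshold affects that baseline as well as the later tests.

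**Stronger readings.** A reader might infer that precision is certainly lost, or that chance imbalance in ability distorts the contrasts. The documents support neither. The first needs a correlation that they do not give. The second holds only conditionally on the allocation that happens to occur, and the standard error already allows for it. Nor does the threshold govern every outcome: mini-BEST and FES-I are not scaled to it, and the control arm has no threshold-based training.

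**Conclusion.** The point holds as a modest efficiency improvement to the primary model. The learning-rate ANCOVA omits the one baseline measure of reactive balance ability that is collected in everyone and that also sets test magnitude and RBT intensity. Whether this costs anything depends on a correlation that cannot be determined from the protocol.

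On the plan's means, SD and 17 per group, omnibus power would rise from about 0.77 to 0.81–0.88 for partial correlations of 0.3 to 0.5, or to about 0.80–0.87 after the 2% variance inflation. There is no net gain below about 0.15 and a very small loss at zero. These figures assume a linear relation with a common slope across arms. Validity is not in question, and the change does not help hypothesis 1: high versus moderate stays below 10% power for correlations up to 0.6. Priority is low.

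**What to change.** In section 2.7, name the baseline multi-step threshold (m/s², continuous) as a prespecified covariate alongside sex in the ANCOVA of learning rate. Adding it to the ANCOVAs of average step count and stepping mechanics, beside the pre-training value, is optional. Mini-BEST and FES-I need no change.

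The cost is one phrase, one degree of freedom per model and about 2% of contrast variance if the threshold proves unrelated to the outcome. No new data are needed. The change should be made before outcome data are seen, since a covariate added afterwards would invite doubt.
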